## Abstract

**Introduction:**

Around 885 000 people live with dementia in the UK, of whom around 50% experience a fall each year. ‘Keep On Keep Up’ (KOKU) is a National Health Service-approved gamified, digital health programme designed to maintain function and reduce falls through strength and balance exercises (Fitness and Mobility Exercise/OTAGO Exercise Programme (OTAGO)), and health literacy games. KOKU has been adapted to the needs of people living with dementia in the community (known as KOKU-LITE). This trial aims to test the feasibility and acceptability of trial processes and usability of KOKU-LITE.

**Methods and analysis:**

A two-arm, parallel, non-blinded feasibility randomised controlled trial will be conducted using mixed methods. Participants aged ≥55 years with any type but varying levels of dementia from mild to moderate stages (ratings 1 and 2 on clinical dementia rating (CDR) scale) and meeting the eligibility criteria will be recruited from patient organisations across Greater Manchester, UK. The target sample size is 60 for the trial. Participants randomised into the intervention arm will use the KOKU-LITE programme for 30 min, 3 times a week for 6 weeks plus dementia-specific falls prevention leaflet and participants randomised into the control arm will receive dementia-specific falls prevention leaflet. Outcome measures: primary outcomes: recruitment, retention and adherence rates; secondary outcomes: quality of life, participants’ activities of daily living, physical activity levels, functional ability, lower limb strength, concerns about falling, falls risk, mood and user’s experience of the technology. Post-intervention interviews or focus groups with participants and health and social care professionals will explore the feasibility of trial processes and technology and evaluate the usability and acceptability of the intervention, respectively. Analyses will be descriptive.

Trial status: the first participants were recruited on 20 March 2024. Data collection is currently ongoing.

**Ethics and dissemination:**

This feasibility trial has been reviewed and received favourable ethical approval from Yorkshire & The Humber—Bradford Leeds Research Ethics Committee, Newcastle upon Tyne (REC reference 23/YH/0262). The findings of the study will be disseminated through peer-reviewed scientific journals, at conferences, publication on University of Manchester, Applied Research Collaboration Greater Manchester and KOKU websites.

**Trial registration number:**

NCT06149702.

STRENGTHS AND LIMITATIONS OF THIS STUDYThis is one of the first studies to test the feasibility and acceptability of trial processes and usability of a gamified digital health application for strength and balance training to reduce falls, functional decline and to improve well-being in people living with dementia in the community (known as KOKU-LITE).Recruiting and retaining people living with dementia can be very challenging and therefore this feasibility study will explore and evaluate different strategies to recruit participants and estimate the time required for recruitment.The barriers and facilitators identified in the recruitment and retention phase of the trial will help us to design a robust definitive trial.We have involved people with lived experience of dementia extensively in the development of KOKU-LITE and will continue to do so in feasibility testing of KOKU-LITE to inform a larger study that will test effectiveness.This feasibility trial is not powered to determine the effectiveness of the intervention.

## Background

 It is estimated that over 885 000 people with dementia currently live in the UK, with this figure anticipated to increase to 1.6 million by 2040.^1^ The total cost of dementia (including health and social care costs, and opportunity costs of unpaid care) in England in 2015 was £23 billion and is predicted to increase to over £80 billion by 2040.^2^ Due to its increasing prevalence, dementia is recognised as an international priority by WHO.^3^

Falls are a public health concern and a common problem in older people (aged 65 years and over). One in three older adults falls each year,^4^ and those with cognitive impairment are more than twice as likely to fall compared with older adults without cognitive impairment.^5^,^7^ In addition, one in five falls causes serious injuries such as fractures or head injuries.^4^ A recent meta-analysis reported that approximately 44.3% of individuals with Alzheimer’s disease experience at least one fall annually, with an average of 1.30 falls per person per year.^8^ The risk is compounded in older people living with dementia (PLwD) due to additional risk factors.^5 9^ Falls are estimated to cost over £4 billion annually to the UK’s National Health Service (NHS).^10^ Evidence related to interventions that are aimed at reducing falls for PLwD was found to be insufficient and inconclusive.^11^,^13^

There is a growing interest in using digital technologies to support PLwD, and the use is recommended by WHO to promote peoples’ health and well-being.^14^ Using digital technology to enable older PLwD to live independently in their own homes for longer, or to prevent falls, has the potential to improve quality of life and deliver cost savings to health and social care.^15 16^ However, there is a lack of robust evidence to suggest effective digital technologies for PLwD. Eost-Telling *et al*, in their systematic review, found no evidence related to the use of apps for falls prevention in PLwD.^17^ A recent study evaluated the feasibility of a digital falls prevention programme (the StandingTall app) for individuals living with dementia and found the intervention to be both feasible and acceptable in this population. However, this study used a pre-post design without a control group and small sample size.^18^ Evidence also suggests that PLwD are reluctant to use digital technologies due to the following barriers: dementia severity, poor or lack of digital literacy, timing and disease progression, technology anxiety, system failures, digital divide, lack of access to or knowledge of how technology works, cognitive fatigue and usability issues.^19^ Hence, it is crucial that digital interventions are designed in a user-centred manner for technologies to be acceptable.^17 20 21^ Digital technologies have the potential to assist relatives/carers of PLwD in predicting, detecting, monitoring and preventing falls in PLwD.^22 23^

‘Keep on Keep up (KOKU)’ is a tablet/iPad-based digital gamified strength and balance exercise programme for older people at risk of falls and functional decline.^24^ KOKU supports older people to engage with simple, progressive exercises, with the aim of helping people remain functionally active for longer and preventing falls. The strength and balance exercises are based on the evidence-based OTAGO and the Fitness and Mobility Exercise (FaME) programme for community dwelling older adults,^25 26^ which have been shown to reduce falls by around a third. KOKU-LITE is General Data Protection Regulation (GDPR) compliant and has The Organisation for the Review of Care and Health Apps^27^ approval for NHS use in the UK. KOKU-LITE is the dementia-friendly version of KOKU.

## Aim

To test the feasibility of the KOKU-LITE digital programme with PLwD aimed at preventing falls and improving well-being compared with control (a dementia-specific falls prevention leaflet).

## Objectives

Explore study recruitment approaches for PLwD, their carers and health and social care professionals (HSCPs) for the feasibility study.Explore the specific training and support needs of PLwD, their carers and HSCPs to enable effective use of KOKU-LITE during the feasibility phase. Particular attention will be paid to the distinct and additional requirements associated with engaging in digital exercises and interactive games on the tablet/iPad, ensuring accessibility and sustained engagement.Explore the usability and acceptability of the KOKU-LITE programme.Describe and determine the suitability of the outcome measures including providing data to permit estimation of effect size to be used in sample size calculations for a definitive trial.

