### Sample size

The total sample size for this study is 75 (60 PLwD for the feasibility study and 15 HSCPs for the interviews).

The intended sample size for the feasibility study will be 30 PLwD in each group, in which simple randomisation will be used with a 1:1 allocation. An attrition rate of 10%–20% is reasonable. A formal sample size calculation is not required as this study focuses on the practicalities of conducting the study. This number is pragmatic to assess the feasibility of the KOKU-LITE programme with the outcome measurements. It is anticipated that this sample size will provide sufficient information to inform a future definitive trial, assuming that the KOKU-LITE programme proves feasible and acceptable for PLwD.^35^

Up to 15 carers and HSCPs (including GPs, geriatricians, clinical psychologists, psychiatrists, community psychiatric nurses, community nurses, physiotherapists, occupational therapists and music therapists) will be recruited to evaluate the usability and acceptability of the app for this target population.

Feasibility of the KOKU-LITE intervention will be assessed based on the feasibility criteria outlined in table 1.^35^,^38^

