### Analysis

#### Quantitative research

Analysis will be descriptive. Baseline characteristics and postintervention data will be summarised, as appropriate, using means (with SD) or median (IQR). For dichotomous or categorical data, frequency will be reported by number or percentage of responses within each category. Calculations will be conducted using SPSS V.29.

As this is a feasibility study, formal hypothesis testing will not be conducted for secondary outcomes, which include changes in health-related quality of life, ADL, physical activity, functional ability and other fall-related measures. Instead, intervention effects will be summarised using point estimates and their corresponding SDs. These estimates will be calculated as the unadjusted mean differences between baseline and each postintervention timepoint. The resulting summary statistics will inform sample size calculations for a future definitive trial, if progression criteria are met. Basic statistical comparisons of pre-intervention and post-intervention outcomes will be performed to describe trends, applying an intention-to-treat approach to ensure that participants are analysed according to their original group allocation.

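### The definitive trial is to be sized from this trial's own effect estimate, which 24 to 27 participants per arm cannot give with useful precision

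*Protocol article*

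**What the plan says.** The fourth objective of the protocol article (Objectives) covers the suitability of the outcome measures, and includes "providing data to permit estimation of effect size to be used in sample size calculations for a definitive trial". The analysis section (Analysis, Quantitative research) turns this into a procedure. For the secondary outcomes, "intervention effects will be summarised using point estimates and their corresponding SDs". It then defines them: "These estimates will be calculated as the unadjusted mean differences between baseline and each postintervention timepoint". Their use follows: "The resulting summary statistics will inform sample size calculations for a future definitive trial, if progression criteria are met".

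On numbers, the Sample size section says: "The intended sample size for the feasibility study will be 30 PLwD in each group". It adds that "simple randomisation will be used with a 1:1 allocation", and on losses: "An attrition rate of 10%–20% is reasonable". The size is described as pragmatic, with no formal calculation. The strengths and limitations list concedes: "This feasibility trial is not powered to determine the effectiveness of the intervention".

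The article names no minimum important difference, no external effect estimate and no confidence interval for the effect. It does not restrict the next calculation to the SD.

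**The concern.** The article disclaims any ability to determine effectiveness, yet gives the effect estimate a job that needs precision. The required sample size varies with the inverse square of the assumed effect, so a modest error in the estimate becomes a large error in the size of the next trial. An estimate that is too high by chance leads to an underpowered definitive trial. One that is too low leads to an unnecessarily large trial, and a zero or negative one gives no usable sample size.

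Two features add to this. The researchers who deliver the programme also collect the outcomes, and nobody is blinded (Blinding; Data collection, Quantitative research), so the estimate may be biased upward. In addition, the effect is defined as a difference between baseline and follow-up. If that is computed within arm, it mixes any programme effect with change that would have occurred anyway, and it is not the between-arm contrast on which a randomised trial is sized.

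**Working it through.** **Inputs from the article.** 30 per arm; attrition 10–20%; 1:1 simple randomisation; assessments at baseline and 6 weeks.

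**Inputs assumed, because the article gives none.** Two-sided 5% level, 80% power, and a true standardised between-arm effect d of 0.2, 0.3 or 0.5 with SD = 1.

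**The plan's own figure.** 2 × 30 = 60 agrees with the stated total. No effect, SD or power lies behind it, so there is nothing further to reproduce. Completers per arm: 30 × 0.9 = 27 and 30 × 0.8 = 24. I use 25.

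**Precision.** SE(d) = √(2/n + d²/(4n)). For n = 25 and d = 0.3, SE = √(0.0800 + 0.0009) = 0.284, and 1.96 × 0.284 = 0.56.
- Observed 0.3: 95% CI −0.26 to 0.86.
- Observed 0.5: 95% CI −0.06 to 1.06.
- With 30 per arm and no losses, the half-width is still about 0.51.
- With baseline adjustment at n = 25 and an assumed correlation r, the half-width is 1.96 × √(2(1 − r²)/25): 0.48 at r = 0.5 and 0.40 at r = 0.7.

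**What that does to the next trial.** n per arm = 2(1.96 + 0.842)²/d² = 15.70/d². This gives 393 (d = 0.2), 175 (d = 0.3) and 63 (d = 0.5). For an observed 0.3, the point estimate implies 175 per arm and the upper limit 22. The lower limit implies no sample size, because it is below zero.

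**One example.** If the truth is 0.3 and the pilot shows 0.5, 63 per arm would be planned. Real power is Φ(0.3 × √(63/2) − 1.96) = Φ(−0.28) = 39%.

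**Simulation.** 200,000 pilots per scenario, 25 per arm, each positive estimate used to size its successor:

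| True d | Needed n per arm | Estimate ≤ 0 | Planned n within 25% of needed (all pilots) | Mean real power (positive estimates) |
|---|---|---|---|---|
| 0.2 | 393 | 24% | 7% | 56% |
| 0.3 | 175 | 14% | 11% | 65% |
| 0.5 | 63 | 4% | 18% | 73% |

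At d = 0.3, among pilots with a positive estimate, 39% plan fewer than half the needed number and 27% plan more than double.

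**Hand check at d = 0.3.** Planning fewer than half needs an estimate above 0.3 × √2 = 0.424. P = 1 − Φ(0.124/0.284) ≈ 33% of all pilots, and 0.33/0.86 ≈ 39% of those with a positive estimate.

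**What the trial can estimate.** The 95% CI for a pooled SD from 48 completers is 0.83 to 1.26 times the estimate, and from 54 completers 0.84 to 1.24 times. The one-sided 80% upper limit at 48 df is √(48/χ²₀.₂₀,₄₈) = 1.10 times the observed SD.

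**Estimand.** These figures describe a between-arm contrast, which a definitive trial needs. They do not describe a within-arm change from baseline, which is one reading of the analysis section.

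**The case against.** The wording can be read more mildly. The objective speaks of data that permit estimation, and the analysis section says that summary statistics, which include SDs, will inform the calculation. Neither says that the observed effect will be the sole target difference, and neither excludes an important difference. That softens the charge. It does not remove it, because the objective names effect size as the quantity to be used, and nothing else in the article is offered as the source of the target difference.

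The size of the harm also depends on an effect that the documents do not give. At 0.5 SD the loss of mean power is 7 percentage points (80% to 73%); at 0.2 SD it is 24 (80% to 56%). Hence the range.

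A reader might infer three stronger things that the documents do not support:
- **That the programme would move forward only on a promising estimate, or be dropped on a chance null.** Table 1 lists recruitment, retention, data collection, and engagement and acceptability. No criterion uses an outcome estimate.
- **That the next trial will usually be far too small.** The error runs in both directions, and a sizeable share of pilots would plan more than double the needed number.
- **That the effect estimate is the main product of this trial.** The primary outcomes are recruitment, retention and adherence; effect size is part of the last objective.

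Upward bias from unblinded assessment is plausible, but it is neither quantified here nor included in the simulation.

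**Conclusion.** The point holds as a defect in the stated use of the data. With 24 to 27 completers per arm, the between-arm effect is known only to within about 0.56 SD either way, and baseline adjustment does not rescue it. For true effects of 0.2 to 0.5 SD, a successor sized on the observed effect would be within 25% of the right size in only 7% to 18% of pilots. These figures rest on the assumed effects, a two-sided 5% level, 80% power, 25 analysed per arm, and the observed effect being used directly as the target difference. The definition of the estimate as a change from baseline is a separate ambiguity in the same place.

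Nothing here touches the conduct of the present trial, its primary feasibility outcomes or its progression decision. What is at risk is the size of the definitive trial. The change should be made, but it is not a reason to halt or redesign this study.

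**What to change.** Reword the fourth objective and the sample size sentence in the analysis section so that:
- this trial supplies only the SD of each candidate outcome (for example the one-sided 80% upper limit, about 1.10 times the observed SD at 48 df), the baseline-to-6-week correlation, completeness and attrition;
- the target difference for the definitive trial comes from a minimum important difference justified independently of these data;
- effects are defined explicitly as between-arm differences and reported with 95% confidence intervals, as description only.

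No new data are needed, and since the change concerns only the use of the results, it can be made after data collection. The downside is that the definitive trial may come out larger: using 1.10 times the SD alone raises the sample size by a factor of 1.10² = 1.21, and an independently set difference may be smaller than a favourable pilot estimate.

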## Methods

### Study design

This feasibility randomised controlled trial is a 6-week study comparing the intervention (KOKU-LITE programme+dementia-specific falls prevention leaflet) with control (dementia-specific falls prevention leaflet) in community dwelling PLwD. After assessing participants for eligibility, they will be allocated randomly to either intervention group or control group. Assessments will be performed at baseline and 6 weeks follow-up (figure 1).

**Figure 1 F1:**
[figure not shown]
Consolidated Standards of Reporting Trials (CONSORT) flow chart of Keep On Keep Up (KOKU)-LITE feasibility trial. The flow chart demonstrates the participants’ journey from enrolment to follow-up period. HSCP, health and social care professional; PLwD, people living with dementia.

A purposive sample of participants who have consented to take part in the study will be invited to participate in postintervention interviews. Exploratory data obtained from the interviews will increase understanding of the responses in the questionnaires about the usability and motivation to use KOKU-LITE, and feasibility of recruitment, data collection approaches and completion of outcome measures.

Patient recruitment has commenced in March 2024 and data collection will be completed by September 2025. The study will be reported in accordance with the Standard Protocol Items: Recommendations for Interventional Trials 2012 Statement for protocols of clinical trials^28^ (online supplemental appendix 1) and TIDieR checklist for the description of the intervention (online supplemental appendix 2). The study process is outlined in figure 1.

### Study participants

As this is a feasibility study, we aim to recruit up to 60 participants (PLwD) (with any type but varying levels of dementia from early diagnosis (mild stages) to moderate stages of dementia (with ratings 1 and 2 on CDR scale) (30 participants in each group) to test the feasibility, usability and acceptability of KOKU-LITE, feasibility of the recruitment processes and suitability of the outcome measures. Up to 15 carers and HSCPs (including general practitioners (GPs), geriatricians, clinical psychologists, psychiatrists, community psychiatric nurses, physiotherapists, occupational therapists, community nurses, occupational therapists and music therapists) (or until saturation) will be recruited to evaluate the usability and acceptability of the app for this target population.

### Participant inclusion/exclusion criteria

#### Inclusion criteria

##### PLwD and carers of PLwD

PLwD aged ≥55 years.*Willing and able to give informed consent (assessed by the trained researchers and/or HSCPs).Who lack capacity to consent themselves but can be supported by a carer or an advocate.For people with dementia who lack capacity, their carers will be recruited to support them.Able to speak English.Able to see the tablet/iPad-based app and read instructions with or without glasses.Able to use tablet/iPad safely, as assessed by the trained research staff and/or HSCPs.Able to move indoors without help, and with or without a walking aid.

*We aim to recruit PLwD aged 55 years and older to ensure that ‘younger-older’ adults with dementia, who may be able to use and benefit from a digital intervention despite cognitive, behavioural and psychological changes, are included.^29^

##### Professionals

HSCPs caring for PLwD in the community.

### Exclusion criteria

#### People living with dementia

 Participants with:acute/chronic or uncontrolled medical condition (eg, severe congestive cardiac failure, uncontrolled hypertension, acute systemic illness, neurological problems, poorly controlled diabetes);recent fracture or surgery (within 6 months);orthopaedic surgery (such as hip/knee surgery) in the past 6 months or on a waiting list to have the surgery;heart problems such as myocardial infarction or stroke in the past 6 months;conditions requiring a specialist/exercise programme (eg, uncontrolled epilepsy, or uses a wheelchair to mobilise indoors);severe hearing/visual impairment that cannot be corrected with aids;any other medical condition likely to compromise the ability to use/access the app. Participants currently in hospital or care home. Participants who have limited understanding or ability to speak English.

### Recruitment

#### People living with dementia

*Intervention study*: up to 60 participants (PLwD) (with varying levels of dementia from early diagnosis (mild stages) to moderate stages of dementia) will be recruited. The CDR scale will be used to screen PLwD.^30^ We will work with professional organisations across Greater Manchester, including Dementia United (DU) (DU is Greater Manchester Integrated Care’s programme for dementia), Join Dementia Research (JDR), African Caribbean Care Group, Together Dementia Support, Alzheimer’s Society and Age UK to identify PLwD who are willing and able to participate in the study. The study information, including leaflets and participant information sheet (PIS), will be disseminated on our behalf by DU (established collaboration from previous work), Greater Manchester Mental Health NHS Foundation Trust (GMMH), Age UK, Dementia UK and other patient organisations to their members and the populations that they serve across Greater Manchester.

In addition, we will use snowball sampling (ie, participants will be asked to forward the study leaflet and the PIS to individuals they know who have the same condition) to advertise the study and extend our recruitment to individuals who might not be engaged with third sector organisations. Different formats of the PIS will be prepared (if needed) to accommodate the needs of PLwD. For example, different font sizes and background colours will be used with PIS. Audible versions of the PIS will be provided when required. Participants interested in the study will be advised to contact the research team directly or via their carer (via email) if they are willing to take part in the study. Participants who indicate an interest will then be contacted by the researcher via face-to-face to discuss the study, check eligibility, screen for capacity and answer any questions that participants may have. Assuming participants wish to continue with the study and meet the eligibility criteria, a face-to-face meeting will be arranged either at the participant’s home or a dementia café based on their preference and a time convenient to them. Participants will be sent consent forms (onlinesupplemental appendix 3.1  3.2) in advance of the researcher meeting the them, to ensure they have the opportunity to read the forms and ask any questions. Consent forms will be completed at the participant’s home or at a dementia café based on their convenience.

*Interviews*: up to 15 participants (PLwd) who have expressed an interest to participate in the interview will be contacted by the researcher after the completion of the study via face-to-face or email or telephone based on their preferences to discuss the interview part of the study, and answer any questions that participants may have. All participants will be requested to return the completed consent form (via email or to the researcher for a face-to-face interview) if willing to participate within 1 week of receipt. A follow-up attempt will be made for participants failing to respond within 1 week.

